### ***CANVAS demonstrates advantages of using brain volume as an outcome measure***

Brain volume is an excellent proxy measure of subsequent cognitive outcome [8-9]. In the ADNI and Australian Imaging, Biomarker & Lifestyle Study of Ageing (AIBL) studies, declining total and hippocampal volume are strongly associated with the development of cognitive impairment [8-10]. Brain volume loss precedes and predicts cognitive decline [8]. This is being reflected in the CANVAS dataset, where we are seeing hippocampal volume loss at 3 months reflected in memory measures at both at 3 months and at one year.

### ***Rapid brain volume loss after stroke***

Even within the first 3 months, we have found that brain volume changes are occurring at a much faster rate than controls [1]. Significant hippocampal and thalamic volume loss occurs in this early period, throwing further doubt on the concept that brain volume at 3-6 months after stroke can really represent a true baseline. We have found that there are progressive changes in brain volume after stroke, and this persists 1 year following the event [1]. Patients lose brain volume at greater rates than controls [1]. The hippocampi and thalami appear uniquely vulnerable, as well as prefrontal cortical regions. Hippocampal volumes can decline 5-10% over 1 year. This volume loss is associated with impairment on memory testing. Some patients lose hippocampal volume between baseline and 3 months after stroke, only to recover at 1 year post-stroke. Why do some patients continue to lose brain

volume, and others don't? What aspects of their risk factor profile are modifiable, and what can we treat to prevent this atrophy that precedes and predicts cognitive decline?

### **Physical activity, cognition and brain volume**

Physical activity consistently emerges as a key modifiable factor for brain health. Regular, lifelong aerobic exercise reduces risk of all-cause dementia [11]. We have found an association between physical activity measures and cognition at 3 months following stroke [12]. We found that the percentage of the day spent active was correlated with both memory and executive function (Stroke Society Association meeting, September 2014). Most interestingly, we have also found that physical activity measures are associated with changes to the resting state functional MRI (rsfMRI) derived functional connectivity of the dorsal attentional network – see Figure 1. More time spent active was associated with increased connectivity in the left inferior parietal region, near the intraparietal sulcus: a critical node in the dorsal attention network [45]. Physical activity, especially aerobic exercise, has many benefits, making it difficult to unpack which aspects are most efficacious in preventing brain atrophy and cognitive decline. Activity improves blood pressure control, and can avert conversion from pre-hypertension to hypertension; it reduces inflammatory markers; it increases socialization thereby both increasing social stimulation and reducing the incidence of depression; it improves cardiovascular capacity, improving vascular reactivity, causing cardiac remodeling and increasing left ventricular (LV) diastolic relaxation; it improves insulin resistance, reduces adiposity, increases lean muscle mass and normalises lipid profiles, reducing LDL and increasing HDL cholesterol.

**Figure 1 Physical activity modulates attention network:**

**A:** rsfMRI derived dorsal attention network (DAN) in 64 stroke patients at 3 months (height uncorrected  $p < 0.001$ , FDR cluster corrected  $p < 0.05$ ).  
**B:** Significant modulation with physical activity levels in right inferior parietal lobe adjacent to IPS, a critical node in the DAN.

[figure not shown]

### **Blood biomarkers: BDNF and HbA1c**

Biomarkers, are biological markers of pathophysiological change. Two biomarkers of interest in the realm of stroke and neurophysiological recovery are Brain-Derived Neurotrophic Factor (BDNF) and Glycated Haemoglobin (HbA1c).

**BDNF:** BDNF is a growth factor involved in the development and survival of neurons and neuronal pathways. BDNF exists within the central nervous system and in peripheral circulation. Majority of stroke-related BDNF studies have primarily been undertaken in animal models, revealing a stroke-associated increase in brain BDNF levels which may also be evident in the circulation [13]. In humans, there is evidence that blood serum BDNF correlates with a reduction in cardiovascular risk 90 days post-stroke [14]. In patients with

coronary artery disease, higher serum BDNF levels have been found in patients with better cardiopulmonary capacity and was related to stronger cognitive function [15]. Whether neurological recovery accompanies these improvements is not clear or not well-supported [14]. No study has yet investigated the role BDNF might have in post-stroke recovery using advanced neuroimaging in combination with cognitive assessment, and a targeted exercise intervention.

**HbA1c:** HbA1c reflects 3-month average plasma glucose concentration and is commonly a marker of glycaemic control. In patients with Type 2 Diabetes Mellitus (T2DM), aerobic exercise can reduce HbA1c levels, thereby suggesting improved management of glycaemic levels [16]. Heightened HbA1c concentrations  $\geq 7\%$  appear to show a threshold risk for stroke in people without a history of diabetes [17]. We are currently conducting a study, based at Austin Health, investigating the neurological and neuropsychological outcome of cardiovascular disease in diabetes. There is a strong rationale to explore plasma glucose control in patients who have stroke and the potential benefits of exercise intervention.

Both BDNF and HbA1c can be sampled via blood collection, which is often already being undertaken as a normal part of a study protocol with minimal impact or discomfort towards participants.

### **Genetic and vascular risk factors**

Apolipoprotein E (ApoE) is a glycoprotein responsible for lipid transport in the brain and other organs. It exists in three isoforms (E2, E3 and E4) encoded by three alleles ( $\epsilon 2$ ,  $\epsilon 3$ , and  $\epsilon 4$ ) on chromosome 19. It confers considerable difference in terms of function and associated risk of disease. The  $\epsilon 4$  allele was found to be a significant genetic risk factor in the development of sporadic Alzheimer's Disease (AD) [18]. A single  $\epsilon 4$  allele increases the risk of AD approximately 3 times while two alleles confer up to 12 times the risk compared to non-carriers. It also increases the risk of vascular disease. As a result of impaired cholesterol transport and metabolism, both APOE  $\epsilon 2$  and APOE  $\epsilon 4$  accelerate atherogenesis. There is now evidence that APOE genotype is related to progression of chronic ischaemic white matter lesion load, as well as being associated with increased hippocampal atrophy, and cognitive decline [19, 20, 21].

ApoE will be sampled via blood, once-off at the first assessment visit (2 months post-stroke), as part of the one blood collection procedure. If this cannot be done, for any reason, we will try again at the second (4 months post-stroke) or third (12 months post-stroke) visits.

### **Sleep**

Poor sleep symptoms are both a risk factor and consequence of stroke. Chronic sleep disturbance is associated with inflammatory conditions such as cardiovascular disease [22], and both sleep disordered breathing and snoring are risk factors for stroke in particular [23, 24]. Poor sleep quality is also associated with increased risk of Alzheimer's Disease, cognitive decline, and increased cortical atrophy in community dwelling adults [25, 26]. In first-incident stroke patients, research shows poor subjective sleep symptoms are reported in over 70% of patients, and those with poorer sleep evidenced greater functional impairment across all strength and coordination tests assessed [27]. Further, research shows that poor sleep quality is considered one of the top five risk factors correlated with poor prognosis for ischemic stroke patients between 18-45 years [28]. As such, sleep may be an important

component to stroke rehabilitation, and there is strong rationale to measure sleep changes as a moderator or mediator of improvement in brain health.

### **Diet**

Associations between diet and cognitive decline are strongly suggested in numerous epidemiological studies and interventional trials. In fact, diet is one of the most relevant modifiable risk factors for early cognitive changes in non-demented older people [29]. It has been projected that controlling seven of the most relevant modifiable risk factors, including mid-life obesity, physical inactivity, smoking, low educational attainment, depression, diabetes mellitus, and hypertension, would delay the onset of dementia and reduce its incidence by up to 30% [30]. The consumption of a healthy diet, characterised by high intake of nutrient-dense foods such as fruits, vegetables, legumes and cereals, and low intake of high fat and high sugar foods, has been associated with higher brain volume in older adults [31]. Given the strong evidence demonstrating the importance of diet for brain health, it is imperative to assess diet as a mediator of stroke rehabilitation.

### **Gut microbiome**

An emerging field of significant research interest involves investigation into the function and dysfunction of the gut microbiome, and its associations with brain health [32]. In line with current theories of the gut-brain axis, gut microbiome health has been linked to onset and progression of neurological disorders, and particularly neurodegenerative diseases such as Alzheimer's, Parkinson's, amyotrophic lateral sclerosis, and Huntington's disease [32]. The associations between the gut microbiome and cognition and outcomes following stroke have received less attention.

Previous research calls for treating the gut as the missing link between exercise and neurodegenerative disorders, particularly because it is a changeable ecosystem and can be targeted through a low-cost therapy such as an exercise program. We hypothesise that alterations in gut microbiota (bacterial markers of gut health) will be associated with the rate and extent of post-stroke cognitive decline. Given the links between exercise, diet, stress and gut health, this relationship is also expected to be moderated by (a) PISCES exercise intervention group or physical activity level as measured by subjective physical activity questionnaires and objective physical activity data from 7-day actigraph monitor wearing; (b) dietary composition as measured with a dietary monitoring app over time period; and (c) psychological factors including mood and self-reported quality of life.

### **Emerging themes for current study: aims, primary and secondary outcome measures**

Recurrent stroke; poorly controlled hypertension; low amounts of physical activity, poor sleep: each of these is independently associated with both cognitive decline and brain atrophy. In addition, each of these represent a modifiable risk factor, one that if demonstrated to contribute to post-stroke regional and total brain volume loss could be readily identified and treated.

## **4. STUDY OBJECTIVES**

### **a. HYPOTHESIS**

The hypotheses of this research project are that:

### **Primary hypothesis**

1. Participants who receive the Physical fitness training intervention will have preserved regional and global brain volume at 4 months post-stroke compared to Participants in the Balance training group.

### **Secondary hypothesis**

- i. Brain volume will be correlated with BP and incident brain infarction at 4 months and 1 year post-stroke;
- ii. Incident end-organ disease (silent or recurrent brain infarction, ambulatory blood pressure (BP), and cardiac structural disease) at 4 months and 1 year post-stroke will be reduced by aerobic exercise;
- iii. Incident physical activity levels, normotension, normal cardiac indices, higher aerobic capacity, and better sleep profiles will be associated with preserved brain volume at 4 months and 1 year post-stroke.

## **b. STUDY AIMS**

Using brain volume and brain connectivity measures at one year after stroke, the aims of this research project are:

1. Examine the effects of home-based aerobic exercise intervention delivered at 2 months post-stroke on brain volume 4 months after stroke, and the stability of such effects at 1 year after stroke;
2. Document vascular burden using 3 end-organ effects: incident brain infarction, cardiac diastolic dysfunction, and ambulatory BP;
3. Examine the link between incident physical activity, aerobic fitness, sleep, and brain volume;
4. Examine the effects of exercise on blood pressure and cardiac diastolic function 4 months and 1 year after stroke;
5. Measure the change in BDNF and HbA1c levels 4 months and 1 year post-stroke and if exercise affects these;
6. Examine the association between physical activity, dietary intake, gut microbiome and brain volume.

An additional aim, which has been framed as a sub-study nested within the greater protocol, will enable us to capture any specific factors that influence participation in, or adherence to, post-stroke home-based exercise regimens.

## **c. OUTCOME MEASURES**

Our primary outcome measure is:

- Brain volume at 4 months post-stroke.
- Our secondary outcome measures are several end-organ disease measures:
  - Silent or recurrent brain infarction;
  - Cardiac diastolic function;
  - Ambulatory BP;
  - Blood BDNF and HbA1c;
  - Sleep duration, variability, efficiency, and onset latency;
  - Dietary intake and gut microbiome
- Qualitative:
  - Understand the feasibility of prescribing post-stroke home-based exercise.

## 5. STUDY DESIGN

### a. STUDY TYPE & DESIGN & SCHEDULE

This is a randomised controlled, multi-site longitudinal study of 120 ischaemic stroke participants (aged >18 years) followed for 1 year (12 months) post-stroke, who at 2 months post-stroke receive an 8-week intervention programme of either Physical Fitness training (approx. 60 participants) or Balance training only (approx. 60 participants). The 2 home-based exercise programmes denote the 2 experimental groups into which participants will be randomly assigned. Participant recruitment will take place at the Austin Health, Eastern Health Western Health and, Epworth HealthCare Stroke Units. MRI Brain scanning, cognitive testing, and assessment of aerobic capacity, as well as blood sampling (to determine HbA1c level, BDNF level, APOE status and genetic risk assessment) will be performed at the Florey, Melbourne Brain Centre, Austin Campus; Sunshine Hospital, Western Health, Monash University & Baker Institute, The Alfred Centre. Some assessments (e.g., demographic interview and cognitive test battery) may be conducted at participants' homes to minimise their burden. Participants will be provided with devices to record their activity levels (for 7 days) and ambulatory BP (24 hours) at times around the scheduled study visits. To minimise inconvenience to participants, arrangements will be made to fit the ambulatory BP device on the first part of each study visit so that it can be returned at the second part of the study visit.

Participants will be given a stool collection kit to take home at each of the 2-, 4- and 12-month time-points. Participants will then return the sample to the study site closest to their home (i.e. Florey, Melbourne Brain Centre, Austin Campus; Sunshine Hospital, Western Health, or Monash University, The Alfred Centre) when returning the BP (24 hour) device.

Participants who have a smartphone will be shown how to download the app (Research Food Diary, Xyris Software, Australia) used for dietary assessment. They will also receive printed instructions about the app's basic function. They will be asked to complete a 3-day food diary (2-week days and 1 weekend) in the week following their 2-month, 4-month and 12-month time points, after they have collected a stool sample.

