### Timelines and feasibility

The 8 week intervention will commence at 2 months after stroke (see Figure 1. Experimental design and participant timeline). At the 2 month, 4 month, and 1 year post-stroke time-points,

we will capture brain images with MRI, perform ambulatory BP measurements and cognitive testing, assess aerobic capacity, fit Actiwatches, deliver the 7-day Sleep Diary and sleep questionnaire, and explain how to use the Research Food Diary app (sleep and dietary assessments to be completed at home). Blood samples will be collected at each time-point to check for concurrent changes in levels of BDNF and HbA1c. Additional blood (10ml) will be collected at the first (2 months post-stroke), second (4 months post-stroke), or third (12 months post-stroke) to test for APOE status and genetic risk. Stool samples will be collected by participants at home after each time point and they will be returned by the participant to the study site with the 24-hour BP device.

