| Blood collection         | Clinical protocol: Stroke Units at Austin Health, Eastern Health, Western Health, Epworth Camberwell, and Monash University: The Alfred Centre campus | As per respective inpatient clinical care needs | MRI                                                                              | Baseline; 4 months; 1 year                                                    | 1 per visit                                                                                                       |
|                          |                                                                                                                                                       |                                                 | Blood for APOE genotyping, BDNF, HbA1c, future genetic and blood marker analyses | Baseline (additional 10ml sample taken for genetic testing); 4 months; 1 year | 27ml for 2 month, 4 month and 1 year visit
Additional 10 ml (total=37ml) for 2 month, 4 month, or 1 year visit |
|                          |                                                                                                                                                       |                                                 | Cognitive and Mood Testing                                                       | Baseline; 4 months; 1 year                                                    | 1 set of tests per visit                                                                                          |
|                          |                                                                                                                                                       |                                                 | Home-based exercise intervention (both groups)                                   | Intervention starts at baseline and continues 3 times per week for 8          | 60 minutes per session                                                                                            |

|                                                                 | weeks                                                              |                                                                            |
|-----------------------------------------------------------------|--------------------------------------------------------------------|----------------------------------------------------------------------------|

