| Aerobic capacity test (VO 2 peak graded stress test) | Baseline; 4 months; 1 year                                         | 30-60 minutes total, dependent on individual capacity                      |
| Physical activity monitoring                                    | 1 week after each testing time-point                               | Actiwatch monitors worn for a duration of 1 week                           |
| Sleep monitoring                                                | 1 week after each testing time-point, as well as prior to Baseline | 7-day Sleep Diary and sleep questionnaire (completed at home)              |
| Dietary intake assessment                                       | 1 week after each testing time-point                               | 3-day food diary recorded with Research Food Diary app (completed at home) |
| Gut microbiome                                                  | Baseline; 4 months; 1 year                                         | 1 sample (completed at home)                                               |

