## **XI. Stool sample collection for microbiome analysis**

At each timepoint, participants will be provided with a specimen kit to take home and asked to collect a stool sample. They will be asked to store the sample in the freezer until it can be returned to the facility. Participants will also receive a thermo bag to place the sample in for preservation purposes when returning it to the facility. This will be completed after each timepoint. In the case of Visit 2 (2-month timepoint), participants will complete the stool sample before they begin the exercise intervention.

The samples will be used to determine the effects of exercise on gut microbiome composition, and relationships with cognitive and brain volume change after stroke.

A portion of samples from each participant will be transferred from The Florey or Sunshine Hospital (depending on site) to Monash University for analysis by A/[name] and her laboratory team who will prepare stool samples using reagents and arrange for microbial sequencing.

It is possible that unused portions of stool samples collected in the current study will be tested for other biological markers at some stage in the future. Any further analysis of stool samples not detailed in this Protocol will be raised with Austin Health HREC if/when that time arises.

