## **XII. Dietary intake monitoring**

Dietary intake will be recorded by participants using the Research Food Diary app (Xyris Software (Australia) Pty Ltd.) At the 2 month timepoint, participants who have a smart phone (Android or iOS) will receive information on the app's basic functions and how to record dietary intake on the app. Participants will complete a 3-day food diary (2-week days and 1 weekend) in the week following each timepoint: 2 months, 4 months, and 12 months. At each timepoint, participants will use the feature "share" in the app to send their 3-day food diary to the study nutritionist, who will check the food diary for completion. If any inconsistency is observed, the nutritionist will advise the Project Coordinator, who will contact the participant by phone, and corrections will be performed if necessary. Nutrient analysis will be undertaken using an Australian food composition database, the FoodWorks Professional (v8) software.

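### The baseline food diary is not required to precede allocation or the first exercise session, and at every visit it is scheduled after the stool sample

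*Protocol*

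**What the plan says.** **Diary.** Section 5.a places the 3-day diary "in the week following their 2-month, 4-month and 12-month time points, after they have collected a stool sample". Section 5.d (XII) repeats the window, "in the week following each timepoint: 2 months, 4 months, and 12 months", without restating the order relative to the stool sample. The procedures table in 5.b also puts dietary assessment after each time-point and has no entry before baseline. Sleep, in the same table, is measured "1 week after each testing time-point, as well as prior to Baseline".

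**Stool sample.** Under Timelines and feasibility in 5.a: "Stool samples will be collected by participants at home after each time point". Section 5.d (XI) adds a safeguard for the first sample: "In the case of Visit 2 (2-month timepoint), participants will complete the stool sample before they begin the exercise intervention". No section gives the diary an equivalent rule.

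**Start of exercise.** The 5.b table reads "Intervention starts at baseline and continues 3 times per week for 8" weeks. Timelines and feasibility also puts the start at 2 months after stroke, and the glossary treats baseline as the point at which the intervention is delivered.

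**Allocation.** Section 5.c randomises after the first time-point assessments, and the exercise pack is sent after the first assessment (5.b, Exercise groups and programmes). The text gives no interval from visit to first session. It does not say whether the diary kept at home counts among the assessments that must come before allocation.

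**Use of the data.** Dietary intake and gut microbiome are listed as secondary outcomes in 4.c, and aim 6 in 4.b concerns their association with physical activity and brain volume. Section 3.c names "dietary composition as measured with a dietary monitoring app over time period" as a moderator of the link between gut microbiota and cognitive decline, and elsewhere describes diet as a mediator of rehabilitation.

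**The concern.** Two separate timing questions arise.

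The first is whether baseline diet is truly a baseline. Participants know their group from the programme they are given. If fitness training changes what people eat from the start, a diary kept in the first exercise week already contains part of that change. An analysis that adjusts for that value, or takes change from it, would then remove part of the effect it is meant to estimate. No analysis can recover intake that was never recorded.

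The second is the pairing of diet with microbiome. Food eaten after a sample did not shape that sample. A diary kept afterwards can inform the same-visit relation only so far as it resembles the intake that came before. This matters most where eating may be shifting, around the start and end of the programme.

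**Working it through.** The protocol states no figure on this point to reproduce, so the check sets the scheduled events in order and counts sessions.

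**Inputs**
- Sessions: 3 per week for 8 weeks (5.b).
- Diary window: the week following the time-point, after the stool sample (5.a).
- Required order at baseline: stool sample before first session (5.d, XI); allocation after the first assessments (5.c).
- Gap from the 2-month visit to the first session: not given. Treated here as an assumption and varied.

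**Order that the text fixes at baseline**
1. Visit assessments, then allocation.
2. Stool sample before the first session.
3. Diary after the stool sample.

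Nothing fixes the order of the diary relative to allocation or to the first session. The stool rule does not settle it: a participant can give the sample, start exercising and then keep the diary, and still comply with every stated rule.

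**Overlap of the baseline diary week with exercise**
- Planned sessions = 3 × 8 = 24.
- Take the diary week as the seven days from the visit.
- Gap of 0 days: up to 3 sessions fall in that week; 3 / 24 = 12.5% of the programme.
- Gap of 1 to 6 days: between 0 and 3 sessions, depending on the days chosen.
- Gap of 7 days or more: 0 sessions; the diary precedes exercise, though not necessarily allocation.

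The nominal schedule, with exercise starting at baseline, sits at the 0-day end. The diary occupies only three days of the week, so fewer than 3 sessions may coincide with or precede the recorded days.

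**Diet and stool pairs**
- Same visit: at 2, 4 and 12 months the diary follows the stool sample, so all three same-visit pairs run in that order.
- Across visits: the 2-month diary precedes the 4- and 12-month samples, and the 4-month diary precedes the 12-month sample. These lagged pairs are in the forward direction.

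**The case against.** The strongest reply is that a literal same-day start is hardly possible. Randomisation is stratified by baseline total brain volume (5.c), so the scan must yield a volume first. Bikes are delivered professionally, and the aerobic prescription depends on the graded exercise test (5.b). Timelines and feasibility mentions dietary assessment alongside the other time-point procedures, to be done at home. If it counts as one of the first assessments, the diary comes before allocation. The timeline figure might show the gap, but it was not available for this review. All of this stands against a claim that the trial has no diet value from before the intervention, which a reader might infer from the schedule. The text does not establish that. What remains is that the order is left to circumstance for the diary, whereas the protocol thought it worth fixing for the stool sample.

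A reader might also infer that diet recorded after a sample is useless for explaining the microbiome. That is not supported. Two weekdays and one weekend day within about a week of the sample are a reasonable proxy for usual diet if usual diet is stable, and the stated roles (moderator, mediator, association) do not require the recorded meals to have produced that particular sample. Some pairs across visits also run forward in time.

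Two further extensions fail. It cannot be said that every one of the 120 participants is affected: section 5.d (XII) gives the app instructions to smartphone owners, stool samples are optional (6.d, 9.a), and about 30% attrition is expected (7.d, 8.b). Nor can a percentage loss in the association of diet with microbiome be given, because the documents report no repeatability for the diary and any figure would only restate an assumed correlation.

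Finally, section 8.c sets out no specific diet analysis, so bias through the baseline value is conditional on that value being used as a baseline.

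**Conclusion.** The point holds as a gap in the schedule. The baseline diary is not guaranteed to precede allocation or the first session, so baseline diet may be post-randomisation. Depending on an unstated interval, between 0 and 3 of 24 sessions (0 to 12.5%) fall in the baseline diary week. Any resulting bias also depends on eating changing early with the programme and on the diary being used as a baseline value; neither is quantified in the protocol.

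Separately, at every visit the diary is a later proxy for the intake before the stool sample. This weakens the temporal reading of the same-visit association without invalidating it.

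Both parts concern secondary and exploratory aims. The 4-month brain-volume ANCOVA does not depend on them. This is an inexpensive improvement to measurement timing.

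**What to change.** 1. In 5.a, the 5.b table and 5.d (XII), give the diary the safeguard that the stool sample already has: the baseline 3-day diary is completed before allocation is disclosed and before the first exercise session.
2. Move app set-up to the home visit that already takes place one week before the baseline assessment (5.a, Participant home visits).
3. State that a diary kept after the first session is not used as a baseline diet value.
4. Preferably, at baseline, keep the diary on the days just before the stool sample.
5. Applying that order at 4 and 12 months is optional. It would put the 4-month diary in the last training week, so it would no longer describe diet after the programme. If recording food alters eating, it could also carry that into the sample. If the present order is kept at those visits, describe the same-visit diary as a proxy for usual intake.

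The cost is wording in the protocol and participant instructions, and some app training time at the home visit. The app, the stool kit and the number of diary days are unchanged, and no clinical rule is affected.
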